### Background

- 1. **Innovative Medicines Initiative**

As part of the European Union’s Innovative Medicines Initiative (IMI), a consortium called SAFE-T (**S**afer **A**nd **F**aster **E**vidence-based **T**ranslation) has been established in 2009 to address the urgent need for more predictive and more robust safety biomarkers for drug induced liver, kidney, and vascular injury [1]. SAFE-T is a partnership between participants from the pharmaceutical industry, small to medium sized enterprises, academic institutions and clinical units of excellence. The consortium’s aim is to qualify promising biomarkers to detect and monitor drug- induced kidney, liver and vascular injury in humans using peripheral samples such as blood and urine. The new translational safety biomarkers will allow the identification and management of drug side effects throughout drug development, helping to reduce late stage attrition rates due to unexpected safety issues whilst at the same time improving patient safety.

### Drug-Induced Liver Injury

Many drugs can unexpectedly induce injury to the human liver. These kinds of side effects can be life-threatening and may lead to withdrawal of the drug treatment.

Drug-induced liver injury (DILI) may occur in a dose-dependent way, as is the case for acetaminophen, or as an idiosyncratic reaction and may present as acute liver failure. Acute DILI is a rare event (14 per 100,000) but its unpredictable nature and the possible fatal course make it a major health concern. DILI has been and still is one of the most concerning safety issues in both drug development and during the routine use of therapeutic drugs. DILI has been the most frequent single cause of safety-related drug marketing withdrawals for the past 50 years (e.g., iproniazid), continuing to the present (e.g., ticrynafen, benoxaprofen, bromfenac, troglitazone, nefazodone). Hepatotoxicity discovered after marketing approval has also limited the use of many drugs, including isoniazid, labetalol, trovafloxacin, tolcapone, and felbamate [2]. As of yet, there are limited possibilities to detect or monitor such liver injury.

### Current Signals for Drug-Induced Liver Injury

The signal currently considered most specific for and predictive of severe drug- induced liver injury is an elevation of total bilirubin levels along with clinically relevant elevations of aminotransferase activities (“Hy’s law”). However, sensitivity of this signal is inadequate to support early detection of injury as damage has already reached an extent where the function of the liver is compromised. Changes in aminotransferase activities, particularly ALT, without bilirubin elevations are more sensitive, but not sufficiently specific for DILI. Also these current standard biomarkers are not ideal to thoroughly monitor disease progression and resolution, and they do not allow to reliably predict clinical outcome of liver injury. The absence of suitable detection methods complicates development of new promising medications and is a burden for many approved drugs, which are already in use to treat diseases. Hence, there is a clear need for more sensitive, specific, and robust biomarkers of DILI. Better biomarkers will enable clinical decision-making in terms of safe continuation and discontinuation of drugs during clinical development as well as in routine use of marketed drugs.

### Rationale for this Study

In the context of SAFE-T’s DILI qualification program, the aim of this study is to collect blood samples from patients with acute DILI, and to investigate whether a set of innovative biomarkers (see Section 3.6.2) can improve on the performance of standard biomarkers (ALT and total bilirubin) to predict the outcome of DILI.

A pilot study (called "pilot study 3") was initially performed in a predetermined number of 45 patients. The aim was to calculate the number of centers and the time needed to obtain a total sample size of 500 DILI cases for the core protocol 3A (3A for protocol 3 Amended).

The performance of the innovative biomarkers will be compared with the standard biomarkers (ALT and bilirubin).

### Recovery Outcome

At the end of the follow-up (at 12 weeks), the patient’s recovery outcome will be classified into 3 categories:

[1] **Full recovery**: ALT<2xULN, total bilirubin<2xULN**;**

[2] **Partial recovery** [ALT>=2xULN or total bilirubin>=2xULN, without increase in total bilirubin between D0 and W12] and patients without decrease in total bilirubin but in whom physicians considered that the decrease in ALT (**adaptive response**) allowed re-treatment of live-threatening disease such as non-liver cancer; If a patient has a re-treatment with severe complications as defined in [3] he will be classified as [3].

[3] **No recovery** including **severe complications** [biological severity (increase of total bilirubin between D0 and W12) or clinical severity (morbidity and mortality)].

Rules for dealing with data issues will be clarified in the statistical analysis plan (SAP). For example, if a patient dies from any cause (even if not directly associated with DILI) or is withdrawn/discontinues from the study, the patient’s data will be excluded from the Main Analysis Set but will be classified as per the last available measurement for the purposes of the Full Analysis Set.

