### Terminology

- - 1. **Definition of Pre-treatment measurement**

Pre-treatment measurement is defined in this study as measurement prior to starting the drug treatment suspected of DILI. These data may be rarely available and likely to be restricted to ALT and total bilirubin. Such data will be used by the investigator and the adjudication committee to make a judgment on inclusion of the patient. It will be entered into the database.

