### Criteria for inclusion

Consecutive patients with suspected acute DILI as defined by:

1. ALT activity exceeding 3 x ULN or ALP > 2 x ULN, within the last 4 weeks before the baseline visit
2. When pre-treatment ALT or ALP activity is available and > ULN, an increase of at least 2-fold the pre-treatment level to D0 is required
3. History of drug intake including any prescription drug, over-the-counter drug, recreational drugs (cocaine, ecstasy, amphetamines), herbal medications and food supplements during the 6-12 months prior to the DILI onset,
4. Absence of other known causes of liver injury
5. Patients with age >18 years that are capable of and willing to provide written informed consent

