### Methods

Proper risk assessment and signal detection as early as possible in clinical drug development are crucial to identify any potential of a drug to cause idiosyncratic liver toxicity. Given the time frame of five years for the SAFE-T consortium to achieve adequate qualification of selected liver biomarkers, it is highly unlikely that sample sizes required will be obtained when using Hy’s law only as signal definition.

For cholestatic liver injury cases, cut-off level for alkaline phosphatase will be 2 x ULN [3].

*Causality assessment:* Cases with suspected DILI should be initially ascertained by clinical judgement of the physician in charge and, subsequently, by the evaluation of an adjudication committee based on the following criteria: 1) an appropriate temporal relationship between the intake of the drug and the onset of the event, 2) the improvement of liver damage following the withdrawal of the drug if no fulminant or chronic liver failure is diagnosed, 3) exclusion of other causes of liver disease, 4) relapse following re-exposure when applicable and decided by clinicians in charge (as in chemotherapy cycles), and 5) previous reports of the adverse reaction. Cases will be further evaluated for causality assessment, by application of the Council for International Organizations of Medical Science (CIOMS)/Roussel Uclaf Causality Assessment Method (RUCAM) scale.

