### Endpoints

### Primary Endpoint: Binary Recovery Outcome

The primary endpoint is the category 1 recovery outcome (see Section 1.6.1), that is the "full" recovery at the last visit (W12).

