### Secondary Endpoints: Time to Events

The time from D0 to reaching the following outcomes will be calculated:

1. Full Recovery from DILI;
2. Severe biochemical DILI
3. Severe clinical DILI (i.e. death or liver complications/failure).

Where a patient does not meet the criteria of the outcome, a censored time will be used as the time of last follow-up visit.

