### Subgroups and Special Populations

The recovery outcome for each type of DILI (cholestatic, hepatic or mixed) will be investigated separately. The biomarkers that have the highest AUROC estimates will be qualified as good predictors of recovery outcome for the particular type of DILI that is being investigated. Biomarker thresholds will also be calculated for each type of liver injury.

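### A patient can already meet the primary endpoint at D0, because full recovery is judged on ALT and bilirubin only while entry is allowed on ALP alone or on a value up to 4 weeks old

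*Protocol*

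**What the plan says.** Protocol Section 3.2 admits patients with "ALT activity exceeding 3 x ULN or ALP > 2 x ULN, within the last 4 weeks before the baseline visit". Section 3.6 repeats the ALP route: "For cholestatic liver injury cases, cut-off level for alkaline phosphatase will be 2 x ULN".

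Section 6.1 states that "The primary endpoint is the category 1 recovery outcome", assessed at week 12. Section 1.6.1 defines that category as "ALT<2xULN, total bilirubin<2xULN". ALP appears in none of the three recovery categories.

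Section 6.4 measures time from D0 to several events, the first being "Full Recovery from DILI". Section 7.4 examines the recovery outcome separately in cholestatic, hepatic and mixed injury, and adds: "Biomarker thresholds will also be calculated for each type of liver injury".

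One entry rule does refer to the D0 value: "an increase of at least 2-fold the pre-treatment level to D0 is required". It applies only when a pre-treatment ALT or ALP is available and above ULN. Section 1.7.1 says of pre-treatment measurements: "These data may be rarely available and likely to be restricted to ALT and total bilirubin".

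**The concern.** The entry rule and the endpoint are built on different enzymes and different dates. The endpoint is meant to be a later outcome that a D0 marker predicts. For a patient who already has the full-recovery values at D0, it partly records baseline status instead. That status is defined by ALT and total bilirubin, the two standards that the new markers are meant to improve on (Sections 1.6 and 2.1).

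Two results are at stake. One is the primary AUROC comparison. The other is the cholestatic analysis in Section 7.4, where markers would be qualified, and thresholds set, against an outcome that omits the enzyme on which those patients could be admitted.

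**Working it through.** **Can one patient satisfy both rules at D0?** All values are in xULN. Entry: ALT >3 or ALP >2 within 4 weeks (Section 3.2). Full recovery: ALT <2 and bilirubin <2 (Section 1.6.1). Injury type: R = ALT/ALP, cholestatic if R <2 (Section 3.6.1).

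- *ALP-only entry.* ALT 1.5, ALP 3, bilirubin 1.0 at D0. Eligible on ALP; meets full recovery at D0; R = 1.5/3 = 0.5, cholestatic. With ALT and bilirubin the same at week 12 and no clinical complication, the patient is scored as fully recovered whether ALP is 3 or higher. Any patient with ALP >2 and ALT <2 has R below 2/2 = 1, so this route falls wholly on cholestatic cases.
- *Earlier ALT.* ALT 6 before D0, then ALT 1.6, ALP 1.0 and bilirubin 0.9 at D0. Eligible on the earlier value; meets full recovery at D0; time to recovery is zero.

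**How fast must ALT fall for the second route?** Assume exponential decline over the full 28 days. ALT is below 2 at D0 if its half-life is under 28/log2(starting ALT/2): about 47 days from just above 3, 21 days from 5, 12 days from 10 and 8 days from 20.

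**Does another rule close the gap?** The two-fold rise needs a known, raised pre-treatment value. The Main Analysis Set (Section 5.1) requires confirmed inclusion criteria, not activity at D0. The DILI Patient Analysis Set applies its criteria at D0, which removes the earlier-ALT route within that set, but ALP >2xULN alone still qualifies.

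**Effect on the AUROC.** The protocol gives no affected share, recovery rate or AUROC, so everything here is assumed. Let 5%, 10% or 20% of patients meet full recovery at D0. Let 2% of them, and 25% of the rest, fail to be fully recovered at week 12. Let ALT be lowest in the affected patients and otherwise uninformative. Write a and b for the affected share among recoverers and non-recoverers. Then AUROC of ALT = 0.5 + (a − b)/2.

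| Affected (of 500) | a | b | AUROC of D0 ALT |
|---|---|---|---|
| 5% (25) | 0.049/0.7615 = 0.064 | 0.001/0.2385 = 0.004 | 0.530 |
| 10% (50) | 0.098/0.773 = 0.127 | 0.002/0.227 = 0.009 | 0.559 |
| 20% (100) | 0.196/0.796 = 0.246 | 0.004/0.204 = 0.020 | 0.613 |

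With these patients removed, the value is 0.50 by construction.

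A second set of assumptions gives ALT an AUROC of 0.65 for recoverers not already recovered at D0 and 0.95 for those who are. With 5% to 30% affected, 95% of them still recovered at week 12, and overall recovery of 60% to 80%, affected patients make up g = 0.05×0.95/0.8 = 0.06 to 0.30×0.95/0.6 = 0.48 of recoverers. The pooled AUROC, (1 − g)×0.65 + g×0.95, is then about 0.67 to 0.79.

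**Effect on the comparison.** This depends on the new marker.

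- If it is equally low in the affected patients, its AUROC rises too. The gap between markers is multiplied by (1 − a)(1 − b) = 0.93, 0.87 or 0.74, so a true gap of 0.10 becomes 0.093, 0.087 or 0.074.
- If it is highest in these patients (for example, because it follows ongoing cholestasis) and otherwise uninformative, the first formula changes sign and its AUROC becomes 0.470, 0.441 or 0.387.

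**The case against.** A reader might infer that some enrolled patients do start out recovered, that nothing is left to predict in them, and that the new markers are therefore disadvantaged. The documents do not support any of these.

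- They show that a patient can meet the endpoint at D0, not how many do. Sections 1.7.2 and 1.7.3 suggest that D0 will often be the first on-drug measurement, or may be the first day in hospital, so the earlier-ALT route may be uncommon.
- A patient with low values at D0 can still worsen. Category [3] covers any rise in total bilirubin from D0 to week 12, and clinical morbidity or mortality. Cholestatic injury with bilirubin at or above 2xULN is not scored as full recovery.
- The AUROC figures for ALT say nothing alone about the comparison. The net effect may be attenuation, a penalty on the new marker, or little. Section 7.1 also lists ALP among the standard biomarkers, so ALT and bilirubin are not the only reference there.

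It can also be said that risk sets and events at time zero belong in the statistical analysis plan, which is not at hand. That is fair for the handling. It does not cover the entry rule and the endpoint definition, which the protocol itself fixes and which do not fit together.

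These limits stand as limits on size and direction. None closes the ALP-only route.

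**Conclusion.** The concern holds as a mismatch between definitions. As written, the primary endpoint can be met at D0 by either route, and persistent ALP elevation with ALT and bilirubin below 2xULN is scored as full recovery. Both follow from the text without any assumed rate.

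The AUROC comparison is distorted to the extent that such patients are enrolled. The illustrated shift in ALT's AUROC, from 0.50 to between 0.53 and 0.61, rests on an assumed share of 5% to 20% and assumed non-recovery of 2% and 25%. A net bias against the new markers is not shown. The cholestatic analysis is the most exposed, because every ALP-only patient with ALT below 2xULN at D0 falls into it.

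**What to change.** 1. Run the primary ROC analysis, and form the time-to-recovery risk set, on patients who do not meet the category [1] values at D0. Report those who do as a separate group, with their number. The restriction uses only D0 data, so it adds no selection on later events. The cost is a somewhat smaller primary set: 475 to 400 of 500 under the assumed 5% to 20%.
2. Reconcile Section 1.6.1 with Sections 3.2, 3.6 and 7.4 on the role of ALP in the recovery categories. Whether an ALP criterion is added, and at what level, is for the investigators. Category [3] must stay intact so that the three ordered categories remain distinct. Step 1 does not replace this, because cholestatic patients with raised ALT or bilirubin at D0 stay in the primary set and may still have raised ALP at week 12.
3. Report recovery with an ALP term as a sensitivity analysis, overall and in cholestatic injury. ALP is already collected at each time-point (Section 3.6.3, Data collection), so no new measurement is needed.

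The cost is amendment wording and one further analysis. Settle it before biomarker results are linked to outcomes.

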### Patient Analysis Sets

- 1. **Main Analysis Set**

The Main Analysis Set is defined as the set of subjects who fulfilled the criteria as defined in the main inclusion criteria of the study, after confirmation by the

Adjudication Committee. Note that the special groups (see Section 3.3) included in the study are excluded from the Main Analysis Set.

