### Severe Clinical DILI

- Dies of any cause
- Requires a transplant
- Complications associated with liver complications/failure such as: hepatic encephalopathy, hemorrhage, kidney failure, medical ventilation, circulatory dysfunction and infections.

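### Section 1.6.1 removes deaths and withdrawals from the Main Analysis Set, against Section 5.1 and its own category [3], and lets a death in the Full Analysis Set be read as full recovery

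*Protocol*

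**What the plan says.** Section 1.6.1 (Recovery Outcome) defines three categories at week 12. Category [1], full recovery, is "ALT<2xULN, total bilirubin<2xULN", with no stated requirement that the patient be alive. Category [3], no recovery, takes in a bilirubin rise or "clinical severity (morbidity and mortality").

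The section closes with "Rules for dealing with data issues will be clarified in the statistical analysis plan (SAP") and then gives an example. Its condition covers deaths and departures alike: "if a patient dies from any cause (even if not directly associated with DILI) or is withdrawn/discontinues from the study". Its consequence differs between the two sets, because these subjects' "data will be excluded from the Main Analysis Set but will be classified as per the last available measurement", the second half of which applies to the Full Analysis Set.

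Section 5.1 defines the Main Analysis Set by the main inclusion criteria and confirmation by the adjudication committee. The only removal it names is this: "Note that the special groups (see Section 3.3) included in the study are excluded from the Main Analysis Set". Death and withdrawal are not mentioned.

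The primary endpoint (6.1) is category [1] at W12. Severe clinical DILI (6.3.2) lists "Dies of any cause" first. For time-to-event endpoints (6.4), a patient who does not meet the outcome is handled so that "a censored time will be used as the time of last follow-up visit".

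**The concern.** The study asks whether new markers predict outcome better than ALT and bilirubin. Deaths are among the outcomes such a marker should identify. A rule that removes patients because of what happened after baseline selects on the outcome. A rule that classifies them by their last measurement may put some of them on the wrong side of the primary endpoint.

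The protocol also gives two definitions of its main population. An analysis plan that follows 1.6.1 departs from 5.1, and one that follows 5.1 departs from 1.6.1.

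**Working it through.** **Passages side by side**

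| Question | 1.6.1, categories | 1.6.1, data rule | Other section |
|---|---|---|---|
| Is a death in the main set? | Implied: mortality is in [3] | No | 5.1: no exclusion for death |
| Is a withdrawal in the main set? | Not stated | No | 5.1: no exclusion for withdrawal |
| How is a death classified in the FAS? | [3] | By last measurement | 6.3.2: severe clinical DILI |

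Three things follow.

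1. Under the data rule, no endpoint analysed in the main set contains a death. That includes severe clinical DILI if it is analysed there.
2. Category [1] rests on two laboratory thresholds. A patient whose last ALT and bilirubin were below 2xULN and who then died can be classed [1].
3. Category [2] requires no bilirubin rise from D0. A death with only a D0 sample shows no rise by construction and can be classed [2]. Section 7.1 counts [1] or [2] as recovered.

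**Size**

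The protocol gives 500 patients but no event rates, so there is no figure to reproduce. All inputs below are assumptions.

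*Share of non-recoveries removed*, if all deaths lie among them: deaths / non-recoveries. 5%/20% = 25%; 5%/15% = 33%; 10%/25% = 40%.

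*AUROC.* Let severity L be standard normal and the marker M = rho·L + sqrt(1 − rho²)·e, with e an independent standard normal. Laboratory non-recovery is the top 15% of L, deaths are 5%, and rho = 0.6. Deaths tracking severity are the top of L; unrelated deaths are drawn at random from the rest.

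| Deaths | Counted as non-recovery | Excluded |
|---|---|---|
| All track severity | 0.81 | 0.78 |
| Half unrelated | 0.77 | 0.79 |
| All unrelated | 0.74 | 0.81 |

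I re-ran this and the figures held to about 0.001. Unrelated deaths add to the non-recovery total: with all unrelated it is 15% + 5% × 85% = 19.25%. Holding the total at 15% instead leaves the pattern unchanged (half unrelated: 0.77 counted, 0.79 excluded; all unrelated: 0.72 and 0.82). Other inputs with all deaths tracking severity: rho 0.4 gives 0.71 to 0.68; 10% deaths with 25% non-recovery and rho 0.6 gives 0.79 to 0.75.

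*Last-measurement rule.* Take 20% non-fatal non-recovery with marker AUROC 0.70 and 5% deaths with AUROC 0.80, each against recovered patients. With deaths as failures, AUROC = (0.20 × 0.70 + 0.05 × 0.80) / 0.25 = 0.72. With half the deaths coded as recovered it is 0.70. This also assumes that deaths track severity.

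*Time to recovery.* With constant hazards and 12-week incidences p_r (recovery) and p_d (death), the recovery hazard over 12 weeks is h = −ln(1 − p_r − p_d) × p_r/(p_r + p_d), and one minus Kaplan-Meier is 1 − exp(−h). For p_r = 0.70 and p_d = 0.05: h = 1.386 × 0.70/0.75 = 1.294, giving 0.726 against a true 0.70. With 2% to 10% deaths the range is 0.71 to 0.76. This matters only if recovery probabilities are reported.

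**The case against.** **The rule is only an example, and details go to the SAP.** It is introduced as an example, and a SAP not available here may settle part of it. But the example is worded as a rule and contradicts both the category definitions beside it and Section 5.1. That is a badly fixed rule, not a missing detail.

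**The text does not say that a dead patient has recovered.** This stands in part. The rule says such patients are classified, and the scheme includes mortality in [3]. Full recovery after death is a possible reading of the last-measurement wording, not an explicit instruction.

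**AUROC need not fall.** This stands. The rule covers deaths unconnected with DILI, and 1.6.1 itself expects patients with life-threatening non-liver cancer. A reader might infer that the rule makes markers look worse; the calculation shows that the sign depends on the cause of death. No effect on the comparison with ALT and bilirubin has been shown.

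**The worst outcomes are not all deleted.** This stands. Transplant, encephalopathy or rising bilirubin in patients who remain in follow-up stay in category [3], and deaths stay in the FAS. No section expressly assigns the ROC analysis or severe clinical DILI to the main set, and Sections 1.6.3 and 7 speak of using all of the data. Section 3.3, which analyses the special groups' marker performance separately from the main set, suggests that the main comparison is made there, but this is an inference.

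**Censoring deaths is legitimate.** This stands for what is planned. Section 7.5 describes models with time-dependent biomarker covariates, where censoring deaths gives a valid cause-specific analysis. A reader might infer from 6.4 that time to recovery is wrongly analysed; the protocol plans no recovery probabilities, so that does not follow.

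**Leaving withdrawals out of the main set is a recognisable choice.** This stands as a method: a complete-case main set with last value in the FAS. It does not remove the conflict with 5.1.

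**Conclusion.** The point holds as a contradiction over the main analysis population and the classification of deaths. Section 1.6.1 conflicts with 5.1 on who is in the Main Analysis Set, and its data rule conflicts with its own category [3]. Followed as written, it selects on the outcome, and in the FAS it leaves open a reading in which a death counts towards the primary endpoint.

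The numerical effect is not established. Under the assumed inputs, excluding deaths moves AUROC by a few hundredths in either direction: down by about 0.03 if all deaths track liver severity, and about 0.02 above the counted value if half do not. The stronger claims that AUROC is biased downward, that all severe outcomes are lost, or that the time-to-event analysis is invalid are not supported. The contradiction still needs correcting because it touches the primary endpoint and the main set.

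**What to change.** 1. In 1.6.1, delete the exclusion of deaths so that it agrees with 5.1.
2. State that death from any cause before W12 is category [3], not full recovery, in both sets, whatever the last laboratory value.
3. Add a sensitivity analysis in which only adjudicated liver-related deaths count as category [3].
4. Give withdrawals their own rule. Say in both 1.6.1 and 5.1 whether they belong to the main set, and how their W12 outcome is handled. Multiple imputation from the ALT and bilirubin course is one option, not a correction.
5. Leave censoring of deaths in place for the cause-specific models of 7.5. If recovery probabilities are reported, use cumulative incidence with death and transplant as competing events.

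The cost is amendment wording, some programming, and adjudication of cause of death. The statistical price is that unrelated deaths count as failures in the main analysis and can dilute a liver-specific marker's AUROC (0.81 to 0.74 in the all-unrelated case above), which is why the sensitivity analysis is needed.
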